### Measurements

At the first measurement opportunity, the trial manager and coexaminer 1 carefully follow inclusion and exclusion criteria. Oral information is given again, and consent is signed by the participant and by coexaminer 1. First, the participant answers two questionnaires (short-form McGill Pain Questionnaire (MPQ)^27^ and RAND-36 (RAND-36 Health-Related Quality of Life)),^28^ then stimulation tests (cold pressor test and pressure algometry)^29–33^ are performed followed by pain rating (NRS)^34^ immediately after 1 min and after 3 min. Finally, blood samples for cobalamin (vitamin B_12_), kidney, liver and heart markers are taken. The participant provides an information card about the study’s design, purpose, treatment options and contacts with telephone numbers. The participant is asked about her interest in an interview in connection with the final measurement opportunity. Coexaminer 2 assesses the blood samples and approves the final inclusion. If tests deviate from accepted reference values, the participant is excluded and encouraged to seek medical attention.

After the approved inclusion, an independent chief examiner performs the randomisation. The participant then receives intramuscular injections of the active substance or placebo, once a week for 12 weeks, given by a registered nurse. Before each injection, the participant answers questions in which he or she estimate his or her expected effects of a given drug, desire for pain relief and average pain intensity during the past week (NRS). The participant has the opportunity to postpone the visit for ±3 days, for example, in case of illness or travelling and may miss a maximum of two injections in order to follow per-protocol analysis. Even if the participant is not compliant with the study protocol, the participant may retain the treatment regime for the duration of the study and may be analysed in the main intention-to-treat analysis.

The second measurement takes place after 12 weeks of intervention and three questionnaires (MPQ, RAND-36 and Patient Global Impression of Change (PGIC))^35^ are filled out. The stimulation tests cold pressor test and pressure algometry are performed as well as blood sampling of cobalamin/p (vitamin B_12_). In cases of low cobalamin/p, the participant is encouraged to seek medical attention but is still included in the study.

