#### Numerical Rating Scale

The participants rate their pain intensity on NRS^34^ in connection with the cold pressor test when the participant takes her hand from the water, after 1 min and finally after 3 min. The participants estimate their pain intensity on a scale (NRS) from 0 to 10, where 0 corresponds to no pain at all and 10 corresponds to the worst possible pain. Pain rating is measured in the same way after the pressure algometry test.

The influence of expectation, desire for pain relief and pain variability will be measured before each injection using the same NRS as used for pain ratings. Ratings of expected pain levels will be obtained by asking patients ‘What level of pain do you expect when this treatment starts to have an effect?’ The NRS scale is anchored at the left by the descriptors ‘no pain sensation’ and at the right by ‘the most intense pain sensation imaginable’. Ratings of desired pain relief will be obtained by asking patients ‘How strong is your desire for pain relief?’ The question will be anchored by the descriptors ‘0=no desire for pain relief’ and ‘10=the most intense desire for pain relief imaginable’. Ratings of pain variability will be obtained by asking the participants their average pain intensity that week. These scales have been validated and used in previous studies.^36–40^

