### Statistical methods

The primary endpoint is tolerance time at cold pressor test and will be calculated on the difference between the two groups after 12 weeks and analysed by analysis of variance (ANOVA). Pain thresholds measured by pressure algometry test (Somedic) will be analysed using t-test and ANOVA, similar to the primary variable. Questionnaires (MPQ, RAND-36 and PGIC) will be analysed using Mann-Whitney tests. In cases of minor loss (less than 10%), a mixed model can be used as an alternative to t-test and ANOVA with repeated measurement. For variables with more than 10% loss, imputation of data will be used. Drop-out participants will be described in a specific analysis. Rejection analysis will be performed on the participants who interrupt the study prematurely.

Results will be reported for both intention-to-treat and per-protocol analyses. Intention-to-treat is defined as the participant is placed in the treatment group he or she had been randomised to. Per-protocol is defined as the participant is placed in the treatment group she de facto received and carried out without significant protocol deviations. The per-protocol results will be presented as sensitivity analyses. The participant may miss a maximum of two injections.

Self-reported ratings of desired and expected treatment outcome pretreatment and post treatment will be implemented in linear regression models to predict any of the outcome measures. Repeated ratings of desired treatment outcome, expected treatment outcome and pain variability will be calculated as each participant’s SD from the repeated ratings and implemented in a linear regression model to predict possible outcome measures.

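### The variability predictor is a raw SD of weekly ratings taken across treatment, so steady change in pain is scored as variability; a minor point on a supplementary analysis

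*Protocol article*

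**What the plan says.** Three parts of the protocol article together define this analysis.

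- **Timing.** Under Numerical Rating Scale: "The influence of expectation, desire for pain relief and pain variability will be measured before each injection". Measurements gives the same timing and a schedule of one injection a week for 12 weeks. A complete series is therefore 12 ratings: the first before any treatment, and up to 11 during it. At most two injections may be missed for the per-protocol analysis, which leaves at least 10 ratings.
- **Content.** "Ratings of pain variability will be obtained by asking the participants their average pain intensity that week". Despite its name, the item records a pain level. The expectation item also asks for a level: "What level of pain do you expect when this treatment starts to have an effect".
- **Use.** Under Statistical methods, the series for desire, expectation and weekly pain are each reduced to one figure per woman, namely the "SD from the repeated ratings and implemented in a linear regression model to predict possible outcome measures". No removal of trend, slope term or pre-treatment window is stated, and the outcomes to be predicted are not named. The same section says that "ratings of desired and expected treatment outcome pretreatment and post treatment will be implemented in linear regression models".

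The Outcomes section lists NRS pain, change in NRS pain and pain variability itself among the secondary outcomes. The primary outcome is cold pressor tolerance time.

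**The concern.** An SD measures fluctuation only when the series has no trend. These series run through the treatment period, when the trial hopes that pain will fall and the authors also expect a placebo response. A woman whose pain declines smoothly has no week-to-week fluctuation, yet she receives a large SD. If that SD is then used to predict an outcome that reflects the same decline, part of the association is the decline related to itself. The paper could report that variable pain predicts improvement when all women fluctuate equally. If pain variability is also kept as an outcome in such a model, the regression is circular.

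A second, smaller difficulty concerns timing. A rating of expectation or desire made after treatment has begun may already reflect treatment and early response, so it cannot be read as a prior predictor.

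**Working it through.** **The plan's own figure.** The article gives no figure for this regression. Its only calculation is the sample size: 2 × (1.96 + 0.84)² × (20/20)² = 15.7, so 16 per group, as stated. This point does not touch it. The number used below is the planned total of 40 women.

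**Step 1: SD from trend alone (no assumption about the data).** Twelve equally spaced ratings on a straight line with total change D lie at steps of D/11. The squared deviations of 0, 1, …, 11 from their mean of 5.5 sum to 143, and 143/11 = 13. Hence SD = (D/11) × √13 = 0.328 × D.

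| Smooth change D (points) | 1 | 2 | 3 | 4 | 6 |
|---|---|---|---|---|---|
| Raw SD | 0.33 | 0.66 | 0.98 | 1.31 | 1.97 |
| Residual SD around own line | 0 | 0 | 0 | 0 | 0 |

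**Step 2: trend plus noise.** With independent weekly noise of SD s, the expected squared SD is s² + (13/121) × D². For s = 1 and D = 3 this is 1 + 0.967 = 1.967, a root of 1.40 against a true fluctuation of 1.00.

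**Step 3: false-positive rate.** Assumptions: 40 women; total fall normally distributed between women with SD 1.5; the same true weekly noise for everyone; outcome equal to the fall plus noise of SD 1, so its correlation with the fall is 1.5/√(1.5² + 1²) = 0.83; a two-sided 5% test of the association between raw SD and outcome. Fluctuation has no true relation to outcome.

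| Mean fall (points) | Noise SD 1 | Noise SD 1.5 |
|---|---|---|
| 0.5 | 28% | 13% |
| 1.0 | 61% | 29% |
| 1.5 | 88% | 50% |

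Independent runs of the last row gave 86% to 88% and 47% to 50%. With no mean fall the rate is about 5% to 12%. The average correlation is then nil, because worsening raises the SD as much as improvement does.

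**Step 4: outcomes measured separately, such as tolerance time.** At a mean fall of 1.5 points the rate is 5% if the outcome is unrelated to pain change, and about 11% to 17% at a correlation of 0.3 (noise SD 1.5 and 1). In a variant with ratings rounded and limited to 0–10, a 2-point mean fall and noise SD 1, the rates are 5%, 21% and 70% at correlations of 0, 0.3 and 0.6.

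**Step 5: the same data with trend removed.** With the residual SD around each woman's own line, or an SD from successive differences, the rate stays at about 4% to 6% throughout. Arm has no part in the Step 3 model, so the artefact comes from differences between women. Adding arm to the regression would therefore not remove it.

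**The case against.** The strongest reply is that the high rates need conditions the article does not establish: a clear mean fall over both arms, modest weekly noise, and an outcome that nearly repeats weekly pain change. This is right. The article gives no expected NRS fall and no weekly noise. The NRS section describes outcome pain ratings made after the cold pressor and algometry tests, which is evoked pain and not average weekly pain. Each rate is therefore conditional. Detrending also assumes a linear course, and a slope term would be another route.

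Five stronger readings might be inferred, and the documents do not support them.

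- *The predictor is tied to every outcome by construction.* That holds only for the SD of weekly pain against outcomes that closely track weekly pain change. For tolerance time the link is indirect and may be absent.
- *Expectation and desire are affected in the same way.* Drift inflates their SDs too, but they are different ratings from any outcome, so the link is plausible and no more.
- *All the ratings are made on treatment.* The first precedes any injection.
- *No post-treatment rating exists.* The text schedules these ratings only before injections, and the descriptions of the 12-week and follow-up visits list none. But Figure 1 and the full protocol are not shown, so one may be defined there.
- *A false placebo mechanism will be reported.* The article speaks only of prediction and plans no mechanistic claim.

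What remains is that the plan states the raw SD as its rule. This is not a detail left open for a statistical analysis plan, and Step 1 shows without assumptions that the rule scores trend as variability.

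**Conclusion.** The point holds in a limited form. The raw SD as defined does not measure variability when ratings drift over the 12 weeks; the contamination is 0.328 SD units per point of smooth change. The consequence for the regression ranges from nothing (outcome unrelated to pain change) to a false association in most trials (outcome correlated 0.83, mean fall of 1 point or more, noise SD 1). The article does not allow a choice within that range. The use of ratings described as post treatment needs clarifying; it is not shown to be an error. The randomised comparison, the primary endpoint and the sample size are untouched, so this is a minor point on a supplementary analysis.

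**What to change.** Reword the last paragraph of Statistical methods as follows.

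1. Define variability as the residual SD around each woman's own linear trend, or from successive week-to-week differences.
2. Include treatment arm and the rating before the first injection in the model.
3. Name the outcomes to be predicted, and do not use pain variability as both predictor and outcome.
4. State which rating is meant by post treatment, and report associations with ratings made after treatment has begun as descriptive, not as prior prediction.

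The cost is analysis wording only, on the same data. A residual SD assumes a linear course and uses one more degree of freedom per woman (10 instead of 11 with complete ratings). Successive differences avoid fitting a line but need a rule for weeks with a missed injection.

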### Patient and public involvement

There is no patient or public involvement in this study.

### Ethics and dissemination

The study is registered at the Swedish Medical Products Agency (EudraCT-no 2015-005086-23, appendix 5.1-2020-71076, protocol no 2020-08-17 V.5.0 and ClinicalTrials.gov). The trial was approved by the local ethical committee at Linkoping (EPM; 2018/294–31, appendices 2019–00347 and 2020–04482). The principles of the Helsinki Declaration^41^ are followed regarding oral and written consent to participate, confidentiality and the possibility to withdraw participation from the study at any time. Good clinical practice is followed, with independent regular monitoring by Forum Ostergotland and Linkopings University, including plans for communicating important protocol modifications. The data will be placed in a locked cabinet at the university until the study is completed and the data are to be processed and analysed. Only involved researchers have access to data when they are to be analysed; however, anyone requesting metadata can access the data during 2025–2035. The study started on 6 February 2019, but recruitment was delayed due to the COVID-19 pandemic. Final recruitment is expected to be completed in 2024. The results will primarily be communicated through peer-reviewed journals and conferences.
